### Wait-list control group

Patients randomized to the control group are given a face-to-face health education according to the handbook to maintain their usual healthy lifestyle. Disease-related questions raised by the patients will be directly communicated or answered through WeChat online. Meanwhile, researchers need to ask patients about their conditions twice a week. Patients can exercise the affected limb through exercises including abduction, forward flexion, backward extension, internal rotation, and wall climbing, according to the guideline and standard for the diagnosis and treatment of breast cancer set forth by the Chinese Anti-Cancer Association (2019 edition), and the patients are not asked to conduct other aerobic activities. The supervised Baduanjin exercise for participants will be offered if they wish after the completion of study.

### Study assessments

Cognitive ability and several patient-reported outcome (PRO) questionnaires will be collected as primary outcome and secondary outcomes, respectively. These outcome assessments will be carried out by professional researchers at pre-intervention (T0), 8 weeks (T1), and 12 weeks (T2) during intervention. The most important primary outcome is cognitive ability, which is assessed using Cancer Therapy-Cognitive Function (FACT-Cog). If there is a 7-point improvement in the FACT-Cog PCI score between the groups, then the intervention will be thought to have tended to have a beneficial effect based on minimal clinically important difference (MCID) [32]. Demographic information collected via interview pre-intervention include patients’ age, level of education, and economic status. Disease information is retrieved from medical records by two trained study coordinators ([name], [name]). The schedule of study outcome assessments is outlined in Fig. 2.

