**Method:**

A single-blinded, randomized control trial was designed. The trial will recruit 70 patients with early-stage breast cancer scheduled to receive chemotherapy from Shanghai in China. All participants will be randomly assigned to (1:1) the supervised Baduanjin group (5 times/week, 30 min each time) or the wait-list control group for 3 months. The effect of Baduanjin exercise intervention will be evaluated by outcome measures including subjective and objective cognitive function, symptoms (fatigue, depression, and anxiety), and health-related quality of life at pre-intervention (T0), 8 weeks (T1), and 12 weeks (T2). The PCI score in the FACT-Cog as the primary cognitive outcome will be reported descriptively, while effect sizes and 95% confidence intervals (CIs) will be calculated. The collected data will be analyzed by using an intention-to-treat principle and linear mixed-effects modeling.

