### Data analysis

Demographics and other characteristics will be reported descriptively to summarize the distribution of all variables via the statistics software (SPSS 24.0). The means and SD will be calculated for continuous normally distributed variables and medians and ranges for non-normally distributed variables. Categorical variables will be presented by absolute numbers and percentages. All cases for both baseline and follow-up measurements will be analyzed for the different outcomes. If missing values exceed 10%, we will impute missing values on covariates by using multiple imputation.

According to the intention-to-treat principle, we will compare the number of patients showing post-intervention 7-point improvement in the PCI scores between the intervention group and the control group using Fisher’s exact tests. A linear mixed-effect model for repeated-measures analysis will be used to analyze the changes in cognition such as treatment, time point, and the interaction between treatment and time point. The between-group effect size will be calculated in post-treatment means (dividing the between-group difference with the pooled standard deviation). The effect sizes of 0.20, 0.50, 0.80, and 1.30 represent small, medium, large, and very large effect, respectively [41]. Two-sided significance level for all tests is 0.05.

Linear regression analysis adjusted for baseline will be used to assess the association between changes in cancer-related symptoms (fatigue, anxiety, and depression) and changes in cognitive function. Adherence to the Baduanjin exercise will be noted by adherence rate ((total frequency − absenteeism)/total frequency × 100%).

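### The article judges the primary PCI outcome by incompatible rules and does not say which one decides, or at which model term and time point

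*Protocol article*

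**What the plan says.** Three places in the protocol article deal with how PCI will be judged.

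- **Abstract, Method:** "The PCI score in the FACT-Cog as the primary cognitive outcome will be reported descriptively", with effect sizes and 95% CIs. No test is attached.
- **Study assessments:** "If there is a 7-point improvement in the FACT-Cog PCI score between the groups, then the intervention will be thought" to have leaned towards benefit, by reference to the minimal clinically important difference (MCID). No test, CI condition or time point is attached. The same section introduces the endpoint with "The most important primary outcome is cognitive ability, which is assessed using" the FACT-Cog, and sets the visits "at pre-intervention (T0), 8 weeks (T1), and 12 weeks (T2) during intervention".
- **Data analysis:** the 7 points become a threshold for each patient: "we will compare the number of patients showing post-intervention 7-point improvement in the PCI scores between the intervention group and the control group", by Fisher's exact test. In addition, "A linear mixed-effect model for repeated-measures analysis will be used to analyze the changes in cognition", with treatment, time and interaction terms. A standardised effect size on post-treatment means is also planned. "Two-sided significance level for all tests is 0.05".

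The Sample size section bases the trial on perceived cognitive impairment, with 58 patients for a power of 0.80 and about 70 after 20% dropout. It does not name the test that has this power.

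**The concern.** A descriptive report and a test at 0.05 are different undertakings. A 7-point difference between group means and a difference in the number of patients who improve by 7 points are different quantities. The article uses all of them for one outcome and does not rank them. If they disagree, the conclusion on PCI depends on which is put forward once the data are known. If any significant result may be used, the chance of a false PCI finding exceeds the stated 5%.

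**Working it through.** **Stated figures.** The 58 cannot be reproduced, because the article gives no effect size, SD or test. Solved backwards, it fits a two-sided t-test at 0.05 with a standardised difference of about 0.75. 58 × 1.2 = 69.6, which matches the stated 70. Losing 20% of 70 leaves 56, or 28 per arm, which is used in step 1.

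**Assumptions.** The article gives no SD for PCI and no correlation between visits. All values of these below are assumptions.

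**Step 1: can the rules disagree on the same data?** A simple two-sample comparison stands in for the model contrast. SE = SD × √(2/28), and the 95% CI is the difference ± 2.005 × SE (t with 54 degrees of freedom).

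| Assumed SD | SE | Observed difference | 95% CI | 7-point rule | Test at 0.05 |
|---|---|---|---|---|---|
| 15 | 4.01 | 7.0 | 7 ± 8.04: about -1.0 to 15.0 | met | not significant |
| 9.3 | 2.49 | 5.5 | 5.5 ± 4.98: about 0.5 to 10.5 | not met | significant |

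They can disagree in both directions.

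**Step 2: chance of at least one significant PCI result with no true effect.** Simulation used 20,000 runs per setting, 29 or 35 per arm, three equally correlated visits, SD 10, 14 or 18 and correlation 0.5 or 0.7. The mixed model was approximated by t-tests on change at T1 and T2, a 2-df test for the interaction, and a t-test on each patient's mean for the treatment main effect. Fisher was applied to 7-point responders at T2 only.

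| Result accepted as a finding | Null probability |
|---|---|
| T2 contrast alone | 0.047 to 0.054 |
| Fisher alone | 0.020 to 0.028 |
| T2 contrast or Fisher | 0.059 to 0.068 |
| T1 or T2 contrast | 0.088 to 0.097 |
| T1 or T2 contrast, or Fisher | 0.100 to 0.109 |
| Treatment main effect, interaction, or Fisher | 0.107 to 0.117 |

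For comparison, independent tests would give 1 - 0.95² = 0.0975 for two and 1 - 0.95³ = 0.143 for three. The simulated values are lower for the same number of tests because the tests are correlated and Fisher is conservative.

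**Step 3: only results favouring Baduanjin.** The nominal rate is 0.025. The T2 contrast alone gives 0.022 to 0.027. T1, T2 or Fisher gives 0.048 to 0.054, about twice the nominal rate.

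**The case against.** The best defence is that the 7-point sentence is a benchmark for interpretation. It is hedged, refers to the MCID, stands in a section on assessments, and belongs to a trial that the abstract calls a pilot. On that reading it sits comfortably beside a descriptive report with a CI. It can also be said that the end of treatment is implied: the Fisher comparison and the effect size are described as following the intervention, which lasts 12 weeks. The article names model terms, not separate T1 and T2 tests. Finally, an analysis plan exists (Trial monitoring mentions it) and may fix the hierarchy.

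Much of this stands. Fisher most naturally refers to T2, so no Fisher test at T1 is counted above. If T2 is read throughout, the inflation shrinks to about 6 to 7%. With the terms the article does name, however, it is 11 to 12%.

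The contradiction remains. A benchmark reading may reconcile Study assessments with the abstract, but it does not reconcile the abstract with tests at 0.05. The trial is also presented as more than descriptive: it is sized for 0.80 power and aims to show whether cognition improves. An unseen analysis plan could settle the order, but it would not correct the article's conflicting statements.

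A reader might infer several stronger things that the article does not support:

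- That all the rules operate at 0.05. Only Fisher and the mixed model do; the descriptive report and the 7-point rule carry no alpha.
- That the 7-point rule contradicts the 80% power, because it is met only half the time when the true difference is exactly 7. The Sample size section never ties its power to that rule.
- That several primary endpoints compete. The phrase about the most important primary outcome is loose, but the abstract and Sample size both point to PCI, and Cognitive ability makes patient-reported complaint the main indicator.

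**Conclusion.** The point holds as an inconsistency in the stated text. PCI is reported descriptively in one place, read against an observed 7-point difference in another, and tested in two ways in a third. No statement says which decides, and no deciding model term or time point is named. That the rules can disagree is shown for plausible but assumed SDs of 9.3 and 15.

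The inflation is moderate: about 9 to 10% for T1 or T2 contrasts and 10 to 11% with Fisher added, against 5% for one contrast. It should not be read as a 10% rate of false claims of benefit; counting only results in favour of Baduanjin, the figures are about 5% against 2.5%. These rates rest on the assumed SDs and correlations and on a t-test approximation to the mixed model. They apply only if any significant result would be accepted. The article does not say that it would; it leaves this open.

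**What to change.** State one rule in the abstract, Study assessments and Data analysis, by a dated amendment before outcomes are analysed:

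- The primary analysis is the treatment difference in PCI at T2 (12 weeks, end of intervention) from the planned mixed model, reported with its two-sided 95% CI. Benefit is concluded only if the CI excludes 0 in favour of Baduanjin.
- The 7-point MCID is used only to interpret the estimate and its CI.
- T1, the Fisher responder comparison, the other FACT-Cog subscales and the objective tests are secondary, without a confirmatory claim.

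T2 suits the 12-week programme and the three-month aim. A single T2 contrast returns the type I error to about 5% (simulated 0.047 to 0.054). No patients, visits or measures are added. The sponsor gives up the choice among tests and time points. Timing matters, since Trial status expected completion by 1 June 2021 and the article appeared on 19 June 2021; the amendment settles the question only if it precedes the outcome analysis.

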**Fig. 2 Fig2:**
[figure not shown]
Standard Protocol Items: Recommendations for Interventional Trials (SPIRIT) diagram of enrolment, treatment, and assessments over intervention time

### Cognitive ability

Patients’ subjective feelings are the most relevant measures of clinical significance, and cognitive complaint reported by patients is the main outcome indicator. The Functional Assessment of Cancer Therapy-Cognitive Function (FACT-Cog) was developed by Wagner et al. [33] to assess subjective cognitive function, and revised Chinese version will be used in this study [34]. The scale was divided into 4 dimensions including 37 items: perceived cognitive impairment (PCI), perceived cognitive ability (PCA), evaluation of others, and impact on quality of life (QoL). The higher the score of the overall cognitive impairment, the better the cognitive function. Cronbach’s α coefficient is from 0.87 to 0.96 with good internal consistency.

In addition, the International Cognition and Cancer Task Force (ICCTF) [1] proposed and considered the objective neuropsychological test battery to be the gold standard for evaluating cognitive function of CRCI. The Hopkins Verbal Learning Test-Revised (HVLT-R) [35] is a test used to assess verbal learning and memory. The Chinese version of HVLT consists of a 12-word list, and the researcher will read them aloud. The patient needs to recall as many words as possible for three consecutive learning trials (total recall). After 20 min, the patient will be asked again to recall (delayed recall). Lastly, a list of 24 words will be read by the researcher, and the patient will be required to declare and answer whether the particular word is mentioned in previous list (recognition). At the subsequent follow-up, a parallel version of HVLT (the 12-word list with different words) is applied to replace the original version. In addition, executive function and attention are evaluated by the Trail-Making Test (TMT) [36] and Digit Symbol Substitution Test (DSST) [37], respectively (see Table 1).

**Table 1 Tab1:**

Comprehensive neuropsychological test

### Patient-reported outcomes

Patients will complete several patient-reported outcome questionnaires aimed to evaluate subjective fatigue (Chinese version of the Multidimensional Fatigue Symptom Inventory-Short Form (MFSI-SF-C) [38]), mood (Hospital Anxiety and Depression Scale (HADS) [39]), and health-related quality of life (Functional Assessment of Cancer Therapy-Breast (FACT-B) [40]) (see Table 2).

**Table 2 Tab2:**
[figure not shown]
Patient-reported outcome measures at baseline and follow-up

### Safety

Adverse events occurred during the study should be truthfully recorded in the adverse event record form, including symptoms, occurrence time, duration, and treatment measures. Adverse events were divided into general adverse events, major adverse events, and serious adverse events according to their severity. A report form should be completed for a serious adverse event (SAE). Evaluation parameters include: level 1 (safe and no adverse effects), level 2 (relatively safe, mild adverse effects, and continued training with no need to do any treatment), level 3 (insecure, moderate adverse effects, and continued training after treatment), and level 4 (suspended study due to serious adverse effects). An adverse event that meets the criteria for SAE will be reported to the local Institutional Review Board.

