## Abbreviations

FACT-Cog: Functional Assessment of Cancer Therapy-Cognitive Function
PCI: Perceived cognitive impairment
PCA: Perceived cognitive ability
HVLT-R: Hopkins Verbal Learning Test-Revised
TMT: Trail-Making Test
DSST: Digit Symbol Substitution Test
MFSI-SF-C: Chinese version of Multidimensional Fatigue Symptom Inventory-Short Form
HADS: Hospital Anxiety and Depression Scale
FACT-B: Functional Assessment of Cancer Therapy-Breast
SAE: Serious adverse event
TOC: Trial Oversight Committee

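### The Safety section sorts serious adverse events from other events by severity, so the SAE form can miss events with a serious outcome, and the criteria for the ethics-board report are not listed

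*Protocol article*

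**What the plan says.** All of the relevant text is in the Safety section of the protocol article.

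- **Classes.** "Adverse events were divided into general adverse events, major adverse events, and serious adverse events according to their severity".
- **SAE form.** "A report form should be completed for a serious adverse event (SAE").
- **Ethics-board report.** "An adverse event that meets the criteria for SAE will be reported to the local Institutional Review Board". The article does not list these criteria.
- **Evaluation scale.** A separate four-level scale runs from no effects through mild effects to "level 3 (insecure, moderate adverse effects, and continued training after treatment") and then "level 4 (suspended study due to serious adverse effects").

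The Abbreviations list has only "SAE: Serious adverse event", which expands the term without defining it. The Randomization and blinding, Trial monitoring and Data collection sections mention adverse events or discontinuation but give no other definition of an SAE.

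**The concern.** Severity and seriousness are different properties of an event. Severity grades how intense it is. Seriousness records whether it had, or threatened, a grave outcome, and SAE reporting is meant to follow that. The article places general, major and serious on one ladder and names severity as the sorting rule, so the SAE label rests on an intensity judgement.

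The distinction has practical weight here. Every participant is scheduled for adjuvant chemotherapy (Inclusion criteria), where intense symptoms without a serious outcome and moderate events that lead to admission are both plausible. The trial has no stopping rules (Trial monitoring), so event review and SAE reporting carry much of the safety oversight. Only the assessors are blinded (Randomization and blinding), so a judgement of intensity by a physician or patient may be made with the arm known. At stake is whether the SAE form covers the right events, and whether staff have one rule or two for the same label.

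**Working it through.** No arithmetic applies. The article gives no adverse event rate, and the point does not depend on sample size, power or significance level. The check is whether the stated rules give the same answer as an outcome-based definition, and whether they agree with each other.

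**Step 1: the SAE form.** The only stated basis for the serious class is severity, and the form is required for that class. Crossing intensity with outcome gives four cases:

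| Intensity | Outcome | Class by the severity rule | SAE by outcome? | Agreement |
|---|---|---|---|---|
| Low or moderate | Not serious | General or major | No | Yes |
| High | Serious | Serious | Yes | Yes |
| Low or moderate | Serious (such as hospital admission) | General or major, no SAE form | Yes | **No** |
| High | Not serious | Can be classed serious, SAE form | No | **No** |

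The rule agrees with seriousness only where intensity and outcome go together. It can misclassify in both directions.

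**Step 2: is the word severity just loose?** The four-level scale in the same section is a separate instrument, and its levels also describe what happens to training. Even so, its wording goes from mild to moderate to serious, so serious stands where a severity grade above moderate would stand. That usage supports reading the three classes as an intensity ladder. It does not prove it.

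**Step 3: the ethics-board report.** Its trigger refers to criteria, not to a class. There are two possibilities:

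- The criteria are outcome-based and stand in a fuller protocol. Then an admission for a moderate event goes to the board under the criteria but does not belong to the serious class, and the form and the report follow different rules.
- The criteria are the severity classes themselves. Then the two disagreements in the table apply to the board report as well.

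Neither possibility leaves the section both consistent and correct.

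**Step 4: is another definition given elsewhere?** No other section defines an SAE by outcome, so nothing in the article overrides the severity rule.

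**The case against.** The strongest reply is that the board report is triggered by criteria, not by rank. A journal article commonly leaves the SAE definition to the full protocol, which is not shown, so the absence of a list is not a finding. This stands, and it limits the point. A reader might infer that moderate events leading to admission go unreported to the ethics board; the documents do not show that. What remains is the stated severity rule, which is present in the article and is either wrong or in conflict with the criteria it relies on.

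Other replies also stand:

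- **Oversight committee.** A reader might infer that it sees the wrong set of events. The Trial monitoring section has it review adverse events without restriction to SAEs, and the Safety section requires events to be recorded with symptoms, timing, duration and treatment. A misclassified event would still be on record and open to that review.
- **SAE counts.** A reader might infer that they cannot be compared with other trials. The Data analysis section states no between-arm SAE analysis, and no stopping rule uses the classes, so that harm is speculative.
- **Size.** One could assume that 10% to 20% of the 70 patients are admitted, giving 0.10 × 70 = 7 to 0.20 × 70 = 14. The documents give no admission rate, and this would count every admission. Those for intense events would be SAEs under either rule, so the misclassified subset is unknown and may be small.

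It can also be argued that severity is meant in a lay sense of gravity, under which an admission would rank as serious. The general and major classes are not defined, so the text does not exclude this. But an ambiguity over which events need the SAE form is itself a reason to correct the sentence.

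**Conclusion.** The point holds as a defect in a stated classification rule. The Safety section sorts SAEs by severity and attaches the SAE form to that class, so an event of moderate intensity with a serious outcome can fall outside the form, and an intense event without one can be classed as an SAE. The ethics-board trigger either conflicts with this rule or shares its error.

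The conclusion rests on reading severity in its usual sense of intensity, and on the article containing no other definition. It does not rest on any assumed event rate. The number of events affected cannot be derived from the documents, and no missed report is shown. The primary outcome, the sample size and the efficacy analysis are untouched. The correction is worth making because it is cheap and improves safety reporting.

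**What to change.** Reconcile the Safety section as follows:

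1. For every adverse event in both arms, record two separate fields: serious (yes/no, by standard outcome-based criteria, stated or cited) and severity grade.
2. Tie both the SAE form and the ethics-board report to the seriousness field only.
3. Remove the sentence that obtains the serious class by ranking severity. If general and major are kept as labels, define them apart from seriousness.
4. The Trial status section describes the trial as underway, so apply the seriousness field to events already on the adverse event record forms, as far as the recorded details allow.

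The cost is one sentence in the protocol, one tick-box on the form and possibly a few more SAE reports, plus a single pass through the existing forms for item 4. The change concerns classification and reporting only and leaves the rules on continuing or suspending training as they are.
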